**PROJECT SUMMARY**

| **Full project title** | Platform evaluation | |
| --- | --- | --- |
| **Project aim** | The aim is to assess the impact of the online nutrition platform, distributed through Diabetes UK, on important health and intervention outcomes. | |
| **Project design** | Mixed method approach using descriptive and inferential (where possible) statistics on platform data and surveys. Thematic analyses will be performed on case studies and semi-structured online interviews. | |
| **Project participants** | Project participants are people with Type 1 or Type 2 Diabetes (or at risk) as referred by Diabetes UK through their website. Other stakeholders such as platform developer and Diabetes UK staff (i.e. dieticians) will be interviewed for implementation purposes and expert opinions. | |
| **Project arms** | Surveys will be distributed to examine several health and intervention outcomes before and after using the platform. | |
| **Sample size** | Sample size of data collected through survey and Mixpanel data is estimated to be (estimated n= 200-300), case studies (n=4), semi-structured online interviews (n=24) including up to 3 dieticians working for Diabetes UK and up to 3 platform developer staff members. | |
| **Planned project period** | 12 months | |
| **Planned recruitment start date** | 01/10/2020 | |
| **Planned recruitment end date** | 01/11/2020 | |
| **Planned project end data** | 28/07/2021 | |
|  | **Objectives** | **Outcome Measures** |
| **Primary** | The primary aim is to assess the impact of the online platform on several health and intervention outcomes | Health and intervention outcomes |

# Key Words: evaluation, diabetes, nutrition, app, mixed method

**SCHEDULE OF OBSERVATIONS**

*Table 1: Schedule of Events*

| Procedure | Screening | Data collection | Intermediate summary report | Summary report |
| --- | --- | --- | --- | --- |
| Recruitment through Diabetes UK website | X |  |  |  |
| Informed consent | X | X |  |  |
| Primary health and intervention outcomes – collected through Mixpanel, case studies, semi-structured interviews and surveys |  | X |  |  |
| Intermediate summary report of project results |  |  | X |  |
| Final summary report of project results |  |  |  | X |

**LIST OF ABBREVIATIONS**

| CU Coventry University  GCP Good Clinical Practice  GDPR General Data Protection Regulation  ICF Informed Consent Form  ICH International Conference on Harmonisation of technical requirements for registration of pharmaceuticals for human use.  PI Participant Information  WMAHSN West Midlands Academic and Health  Science Network |  |
| --- | --- |
|  |  |

**PROJECT PROTOCOL**

Platform evaluation

# INTRODUCTION

1.1 Background

The prevalence of Type 2 Diabetes, and the number of people who are at risk for developing this condition, is rising every year. There are 4.7 million people suffering from this condition with 12.3 million people being at risk for developing Diabetes in the UK (Diabetes UK, 2020). Diabetes can have severe long-term health consequences but also increases health care costs (Jönsson, 2002). Diabetes UK (2020) offers an ecosystem with a variety of education tools through their website aimed at people with Type 1 Diabetes, Type 2 Diabetes, those who are at risk for developing Type 2 Diabetes and those who are caring for people with Diabetes. The platform developer developed an innovative personalised nutrition platform to support the delivery of healthy food recipes and meal planning for people with Diabetes.

- 1. Proposed project

This proposed project aims to assess the impact of the platform on important health outcomes and examine intervention outcomes across people with Type 1 or Type 2 Diabetes (or at risk) as referred by Diabetes UK through their website (<https://www.diabetes.org.uk/>). Doing so will allow the West Midland Academic Health and Science Network (WMAHSN) and Diabetes UK to take an informed decision as to whether a business case can be made to support the platform as part of the Diabetes UK ecosystem; and if so, provide supporting information for the business case for further roll-out based on the available evidence and insight gained.

1.3 Project population

Project participants consist of people with Type 1 or Type 2 Diabetes (or at risk) as referred by Diabetes UK through their website. Other stakeholders such as platform developer and Diabetes UK staff (i.e. dieticians) will be interviewed for implementation purposes and expert opinions.

1.4 Treatment / Intervention (if applicable)

The sample consists of people with Type 1 or Type 2 Diabetes or those who are at risk of developing Type 2 Diabetes. People will be compared on health and intervention outcomes before and after using the platform to see if there are differences in outcomes over time. This will allow to make within group comparisons using descriptive and inferential (where possible) statistics.

# 2. RATIONALE

- 1. Aims and hypothesis

This project aims to assess the impact of the platform on important health outcomes across those diagnosed with Diabetes Type 1 or Diabetes 2 (including those who are at risk for developing Type 2 Diabetes). Intervention outcomes will also be examined. There are no specific hypotheses formulated for the current project.

- 1. Justification

This proposed project aims to assess the impact of the platform on important health outcomes and examine intervention outcomes across people with Type 1 or Type 2 Diabetes (or at risk) as referred by Diabetes UK through their website (<https://www.diabetes.org.uk/>). Doing so will allow the West Midland Academic Health and Science Network (WMAHSN) and Diabetes UK to take an informed decision as to whether a business case can be made to support the platform as part of the Diabetes UK ecosystem; and if so, provide supporting information for the business case for further roll-out based on the available evidence and insight gained.

## Assessment and management of risk

## There are no ethical issues or significant risks that the project may lead to physical or emotional distress to participants or researchers or cause any reputational damage to the stakeholders involved. Given the research portfolio of Coventry University (CU) and that all project members are aware of the CU disclosure protocol, Code of Conduct and trained according to Good Clinical Practice (GCP) guidelines no management issues are expected. Also, the project includes a relatively small samples size compared to traditional trials which lowers the risk on management issues.

3.2 Primary endpoint/outcome

The primary outcomes are categorized as follows: (1) Outcomes directly related to the health status and condition management of the participants (e.g. weight, BMI, HbA1c, blood pressure, waist, generic health status, smoking yes/no, confidence in diabetes management and meal planning, healthy eating) and (2) Outcomes directly related to platform intervention usage:

- Number / Duration of sessions
- Number of users / average sessions per user
- New users
- Monthly Active Users / Weekly Active Users
- Specific actions:
  - # Recipes Viewed, (any indication on favourite content)
  - # Recipe Added / Saved
  - # Meal Plans created
  - # Shopping Actions
    - Carts sent online
    - Meal plans sent to cart
    - In store shopping actions - print, email, sms, app, etc.
    - Number of items shopped / value
- Platform used - app vs web app
- GA audience metrics: Demographics, Geography,
- User Retention
- Top 20 recipes (potentially)
- The average or typical meal plan including health score (potentially)

Additionally, expectations beforehand and satisfaction afterwards will be assessed. Diabetes UK will collect data regarding their traffic on the website and the amount of referrals to the online platform.

# 4 PROJECT DESIGN

Health and intervention outcomes within the intervention group (before and after completing the platform) will be examined using a mixed-method research approach consisting of descriptive and inferential (where possible) statistics on surveys, Mixpanel data as well as thematic analyses on case studies and semi-structured online interviews.

# 5 PROJECT SETTING

The project will run fully online using Microsoft Teams application (including recording, storing and screen share options) where CU will invite participants for case studies and semi-structured interviews. This is seen as a good, safe and secure environment which will be comfortable and have ease of access for both participants and research staff.

**6 ELIGIBILITY CRITERIA**

The population consists of people with Type 1 or Type 2 Diabetes (or at risk) as referred by Diabetes UK through their website. Other stakeholders such as platform developer and Diabetes UK staff (i.e. dieticians) will be interviewed for implementation purposes and expert opinions.

**6.1 Inclusion criteria**

Project participants:

- Diagnosis Type 1
- Diagnosis Type 2 or at risk for Diabetes Type 2
- Relatives taking care of people with Type 1 or Type 2 Diabetes (or at risk)
- Good understanding of written and spoken English language

Platform development staff: Good understanding and know-how of platform and current project

Diabetes UK staff: Qualified and experienced dieticians working with people having Type 1 Diabetes, Type 2 Diabetes or those who are at risk for developing Type 2 Diabetes.

**6.2 Exclusion criteria**

There are no specific exclusion criteria formulated for the current project.

# 7 TRIAL PROCEDURES

Diabetes UK will refer potential participants through the Diabetes UK website to the platform where they can sign up, giving consent to platform terms and conditions as they sign in to use the Wisk platform whether or not they want to participate in the research (choosing not to participate in the research will not stop them from using the platform). They are also asked to give permission to share their email address and Mixpanel data to be passed on to the lead CU researchers allowing them to contact participants as part of the wider research project. It must be noted that when participants only want their email address to be shared and not their platform usage data they will still be able to participate into the research by filling in the two surveys as Mixpanel data would be labelled as missing at that point. The plaform developers will send email addresses of new users to lead CU researchers in a shared OneDrive folder with weekly updates. Mixpanel data, with email address as an identifying variable for each user, will be shared in a shared OneDrive folder on a weekly basis.

The lead CU researchers will send an invitation email to participants to fill in the first survey (please see Attachment 1) with enclosed Participant Information (PI; please see Attachment_2) and Informed Consent Form (ICF; please see Attachment_3) explaining the project aim, related activities and burden in terms of duration. The email will contain a link to the first survey (hosted by Qualtrics; please see Attachment_4) in which both PI and ICF are embedded. Two automated reminder emails will be send by Qualtrics in cases where participants do not fill in the first survey, one after a week of non-response, and one after two weeks of non-response. All data will be deleted in case there is non-response after the three emails. If participants do not want to be contacted or receive any reminder emails they can email they would like to UNSUBSCRIBE. Each participant will be provided with a unique survey link that recognises each participant by a unique response number only. The end of the first survey will present the option if the participant is (1) willing to participate into a prize draw (using their email address) and (2) willing to participate in follow-up research so selected participants can be approached for the case studies or semi-structured online interviews. After 8 weeks of using the platform, participants will receive an invitation email (please see Attachment_5) to fill in the second survey (please see Attachment_6).

Based on platform usage data (low vs. high engagement) and provided consent at the end of the first survey, participants will be selected for further research activities which consist of case study and semi-structured online interviews. Participants selected for the case study interview will receive an invitation email (please see Attachment_7) with PI (please see Attachment_8) and ICF enclosed. Participants who are willing to participate into the case study interview will sign the ICF (please see Attachment_9) and send it back to the CU lead researcher. Participants who prefer a phone interview can indicate this in an accompanying email. The case study interview outline is presented in Attachment_10.

Participants selected for the semi-structured interview will receive an invitation email (please see Attachment_11) with PI (please see Attachment_12) and ICF enclosed. Participants who are willing to participate into the semi-structured interview will sign the ICF (please see Attachment_13) and send it back to the CU lead researcher. Participants who prefer a phone interview can indicate this in an accompanying email. The semi-structured interview outline for service-users, platform developer staff and Diabetes UK staff is presented in Attachment_14.

The case studies and semi-structured interviews will be performed online through the Microsoft Teams application, supporting screen sharing as well as recording while using a Dictaphone for back-up recording. Data files will be automatically saved in Microsoft Streams and files recorded through the dictaphone will be stored immediately after the interview in a dedicated Onedrive folder so the recording can be deleted from dictaphone. Data will be destroyed after three years from project start date. Please see Figure 1 for the process of data sharing.

- 1. **Recruitment**

The sample will be recruited by Diabetes UK through their website (<https://www.diabetes.org.uk/>) supported by exposure through social media (e.g. <https://twitter.com/DiabetesUK>). The Diabetes UK website which will refer participants to the platform and accompanying opportunity to participate into the research project. The platform developer and CU will use their Twitter accounts to retweet messages from Diabetes UK. Recruitment will continue till 01/11/2020 so there is enough time to include the final participants into the analyses and therefore final report. Recruitment rates will be reviewed on a weekly basis*, allowing DiabetesUK to take action to promote the project further if required, or the recruitment time could be extended to allow for further new users and survey completions. Please see Attachment_15 for Diabetes UK transparency statement.

*To review recruitment rates, project partners will complete the spreadsheet below on a weekly basis:

[figure not shown]

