**Device Usage**

1. On what device do you use the platform?

□ On an Android smartphone/tablet

□ On an Apple iPhone/iPad

□ On a computer with internet

2. Do you have mobile internet and/or wifi on your computer/smartphone/tablet?

□ Yes, I have mobile internet

□ Yes, I have wifi connection

□ Yes, I have mobile internet and wifi connection

□ No, I have none of them

3. For what purpose do you use your computer/smartphone/tablet the most?

□ Social media (like facebook, twitter, instagram)

□ Call/text/whatsapp

□ Listen to music (like Spotify, Youtube)

□ Search for information (like Google)

□ Other, please specify_________________________

4. Do you use your computer/smartphone/tablet to monitor and/or improve physical activity?

□ No

□ Yes, please specify_________________________

5. Do you use your computer/smartphone/tablet to monitor and/or improve your nutrition?

□ No

□ Yes, please specify_________________________

6. Do you use your computer/smartphone/tablet to monitor and/or improve your blood glucose level?

□ No

□ Yes, please specify_________________________

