**Thank you for filling in the first survey.**

You will be send a link to the second survey (hosted by Qualtrics) in 8 weeks.

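### The 'before' survey is sent only after users have platform access, and the 8-week follow-up is worded with two starting points, so the before/after-use comparison is not guaranteed

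*Combined protocol and SAP*

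**What the plan says.** Section 1.4 sets the contrast: "People will be compared on health and intervention outcomes before and after using the platform". Section 8.3.2 repeats it as the primary outcome analysis.

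Section 7 gives the order of events. Users join by "giving consent to platform terms and conditions as they sign in to use the Wisk platform", and "choosing not to participate in the research will not stop them from using the platform". Contact details then move in batches: "The plaform developers will send email addresses of new users to lead CU researchers in a shared OneDrive folder with weekly updates". The researchers email the first survey after that, and section 7.2 confirms that they approach people who have already signed up. Reminders go out "one after a week of non-response, and one after two weeks of non-response". Section 7 says data are deleted if there is no response after three emails, but gives no closing date after the last one.

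The second survey has two timings. Section 7 says: "After 8 weeks of using the platform, participants will receive an invitation email". The closing text of the first survey (Attachment_4) says: "You will be send a link to the second survey (hosted by Qualtrics) in 8 weeks". The second survey (Attachment_6, System Usability Scale block) asks how often the platform was used over an eight-week span without saying when that span starts.

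The first survey also asks, in the present tense, "On what device do you use the platform".

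**The concern.** A before/after comparison with no control group depends on a baseline that comes before exposure and on a known interval to follow-up. The plan secures neither. Access starts at sign-up, the baseline comes later by a variable amount, and the two statements of the follow-up trigger agree only for someone who completes the first survey on the day that use begins.

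At stake is what the reported change means. For anyone who used the platform before answering, part of any early benefit may already be in the baseline. Expectations, a planned moderator in sections 7.5.1 and 8.4 that section 3.2 wants assessed beforehand, may already reflect experience. The result is meant to inform a business case for wider roll-out (sections 1 and 2), and the within-person change is its main quantitative evidence.

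**Working it through.** The plan gives no figure for this delay, and section 8.1 says the sample size was not derived statistically, so there is no stated calculation to reproduce. The check is timing arithmetic.

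**Inputs**
- Email transfer: weekly (section 7), so 0 to 7 days after sign-up.
- Reply: at once, at the first reminder (7 days) or at the second (14 days) (section 7).
- Follow-up: 8 weeks = 56 days (section 7; Attachment_4 closing text).
- Assumptions: access runs from sign-up, and invitations go out as soon as emails arrive. A reply 7 days after the second reminder is added as an assumed extra case, because no closing date is given.

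**Formulas**
- Lag L = transfer + reply time. Maximum at the second reminder: 7 + 14 = 21 days. Assumed extra case: 7 + 21 = 28 days.
- Rule A (clock starts at use, section 7): days between surveys = 56 − L; total access = 56; share of access before baseline = L/56.
- Rule B (clock starts at the first survey, Attachment_4): days between surveys = 56; total access = 56 + L; share before baseline = L/(56 + L).

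| L (days) | A: between surveys | A: share before baseline | B: between surveys | B: total access | B: share before baseline |
|---|---|---|---|---|---|
| 0 | 56 | 0% | 56 | 56 | 0% |
| 7 | 49 | 12.5% | 56 | 63 | 11.1% |
| 14 | 42 | 25% | 56 | 70 | 20% |
| 21 | 35 | 37.5% | 56 | 77 | 27.3% |
| 28 (assumed) | 28 | 50% | 56 | 84 | 33.3% |

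These are invitation dates. Actual second-survey completion dates will vary further under either rule.

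**Effect on the estimated change.** Suppose, for illustration, that a benefit builds at a constant rate from sign-up. Under Rule A with L = 21, the surveys capture 35/56 = 62.5% of the 8-week change. Under Rule B they capture 56 days' worth whatever L is. Rule B loses effect only if the benefit comes early. Section 7.5.4 gives a case where that could happen: a user who prints the recipes at the first visit and has no need to return.

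**Which outcomes.**
- Most exposed: general health and healthy eating, which are asked as current states in both surveys, and possibly weight and waist.
- Less exposed: HbA1c, blood pressure and cholesterol, which are requested as the latest available values with dates and may pre-date sign-up.
- A separate matter: confidence. It is rated as a level at baseline but mainly as agreement that the platform raised it at follow-up, so there is no clean change score to attenuate.

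**The case against.** The strongest reply is that the delay may be small and its effect limited. Twenty-one days requires sign-up just after a weekly transfer, a reply only at the second reminder, and real use from the first day. Prompt responders may have used the platform little or not at all, and signing up is not the same as using it. No response-time distribution is given. This stands: 21 days is the far end of a 0 to 21 day range, not a typical value.

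A reader might infer that the before/after change is biased towards zero in general. The documents do not support that. The interval shortens only under Rule A, Rule B needs an early effect, and several outcomes are largely outside the problem.

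A reader might also infer that the expectation subgroup analysis is circular. It is not: the expectation items in Attachment_4 look forward and are not derived from the outcomes. Early use could colour them, which is a weaker fault. The present-tense device item is only mild evidence, since someone who has just signed up could answer it.

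Nor is exposure wholly unobserved. Mixpanel data arrive weekly, and section 8.3.2 relates usage to health outcomes where possible. But those data are missing for people who decline to share them, and no analysis uses them to define a clean baseline or adjust for the lag.

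The invitation emails, the participant information and the data-sharing flowchart are not in the text reviewed and may add timing detail. They cannot remove the conflict between section 7 and the survey's closing text. That the project is exploratory, without hypotheses or a statistical sample size, lowers the stakes but does not define time zero.

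**Conclusion.** The point holds in a limited form. By design the baseline follows access, with no gate, no maximum lag and no first-use date in the survey, and the follow-up trigger is worded with two origins. The lag is 0 to 21 days for replies up to the second reminder, and longer if replies come later. Rule A leaves 35 to 56 days between surveys, with up to 37.5% of access before baseline. Rule B fixes the invitation interval at 56 days but lets total access run from 56 to 77 days.

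For users who start before answering, a genuine benefit on quickly changing self-reports may be understated, subject to the conditions for each rule shown above. How many users this affects, and by how much, cannot be determined from the documents. The order of events and the conflicting wording are certain; the size of any bias is not.

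**What to change.** 1. **Baseline at sign-up.** Offer the first-survey link, with the participant information and consent form already embedded in it, on the sign-up page. Keep the unique participant identifier, and use the emailed link as the reminder.
2. **First-use date.** Add an item to the first survey asking whether the platform has already been used and, if so, from what date. Back it with Mixpanel for those who share their data.
3. **One trigger.** Send the second-survey invitation 56 days after first-survey completion. Align section 7, the closing text of Attachment_4 and the recall question in Attachment_6 to that rule.
4. **Analysis (section 8.3.2).** Keep all paired surveys in the main analysis. Report the lag from first use to baseline and the interval between surveys. Add a sensitivity analysis of the before/after and expectation results, limited to baselines completed before first use or adjusted for the lag. Restricting the main analysis to early responders would select on response speed, so the restriction belongs in the sensitivity analysis.

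Cost: a small change to the sign-up page with handling of duplicate links, one survey item, aligned wording in three places and one extra analysis.

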7.1.1 Patient identification

Diabetes UK will refer potential participants through the Diabetes UK website to the platform where they can sign up, giving permission to share Mix panel data (including their email address), to be passed on to the lead CU researchers allowing them to contact participants as part of the wider research project. The lead CU researchers will send an invitation email to participants with enclosed Participant Information and Informed Consent Form explaining the project aim, related activities and burden in terms of duration. Once participants provided informed consent electronically, survey questions will be shown for which a reminder will be send two times to non-responders (unless they reply on the email by unsubscribe) by an automated setting through Qualtrics. The first part of the survey will verify diagnosis (e.g., Type 1, Type 2, at risk or other) and sufficient understanding of verbal/written English language would be derived from completing the consent form.

- - 1. Screening

For the current project no laboratory or diagnostic testing is involved in the above-mentioned inclusion criteria. Therefore, no specific duration between screening and recruitment is expected. Based on the current inclusion/exclusion criteria, no participants will be expected to be subject to rescreening.

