**8.2 Planned recruitment rate**

The planned recruitment rate for case study interviews is four participants and 24 participants for the online semi-structured interviews depending on the availability of platform developer staff (n=3) and Diabetes UK dieticians (n=3). All participants (anticipated n=200-300) will be approached to fill in a *before* and *after* survey. Overall, it is expected that more participants will be approached than mentioned above as nonresponse should be taken into account.

- 1. **Statistical analysis plan**

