**8.6 Procedure(s) to account for missing or spurious data**

The semi-structured interviews and case studies will be video and audio recorded. Participants will be informed that they may withdraw any time up until the point that their data is anonymised for analysis. At this point the researchers will not be able to identify their data for withdrawal. This date will be two weeks after the semi-structured interview / case study has taken place and will be mentioned in the Participant Information.

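### No reminder is stated for the 8-week survey and section 8.6 has no procedure for unreturned surveys, so the before-after change falls on people who return both, and usage results may cover survey responders only

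*Combined protocol and SAP*

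**What the plan says.** **Reminders.** Section 7 (Trial Procedures): "Two automated reminder emails will be send by Qualtrics in cases where participants do not fill in the first survey", after one and two weeks without a reply. For the second survey the same section says "After 8 weeks of using the platform, participants will receive an invitation email", and no reminder follows. Section 7.1.1 says "survey questions will be shown for which a reminder will be send two times to non-responders", but it is describing the survey that opens after consent and checks the diagnosis, which is the first. Section 7.2 mentions a reminder only in connection with the decision to take part.

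**Deletion.** Section 7: "All data will be deleted in case there is non-response after the three emails". The three emails are the first invitation and its two reminders. By then CU may already hold usage data, because "Mixpanel data, with email address as an identifying variable for each user, will be shared in a shared OneDrive folder on a weekly basis".

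**Analysis.** Section 8.3.2 compares health outcomes before and after platform use within one group, and relates usage to health outcomes where possible. Section 3.2 lists usage measures among the primary outcomes, including "Number of users / average sessions per user", active users and retention.

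**Missing data.** Section 8.6 covers the recording of interviews and case studies and the withdrawal rule: "Participants will be informed that they may withdraw any time up until the point that their data is anonymised for analysis". It does not mention unreturned surveys or blank items. Section 8.5 adds only that usage data which a participant did not agree to share count as missing. Section 8.2 recognises non-response but gives no rate and no method.

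**The concern.** A paired before-after comparison with no control group needs both surveys from each person. The second survey is where pairs are lost, yet it has the weaker stated follow-up, and nothing says what happens to people who answer once. By default the analysis uses those who return both.

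If willingness to answer goes with liking or using the platform, the estimated change is higher than the change among all users. The same applies to retention and sessions per user if they are computed on a file from which first-survey non-responders have been removed. Section 1 says the results will inform a decision on a business case and further roll-out. Readers of the report would therefore need to know whom the figures describe.

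**Working it through.** **1. Inputs.** Section 8.1 says the sample size was not derived statistically. No response rate, effect size or standard deviation is given, so there is no planned figure to reproduce. Every rate below is an assumption, and changes are in SD units of the change score.

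**2. Selection over two surveys.** Assume half of users are highly engaged with a true change of 0.30 and half have no change, so the all-user mean is 0.5 × 0.30 = 0.15. Let h and l be the response rates of the two halves, the same at each survey. The highly engaged share is h/(h + l) after survey 1 and h²/(h² + l²) after both. The mean change is 0.30 times that share.

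| h / l | Share after survey 1 | Share after both | Mean change, survey 1 responders | Mean change, both returned |
|---|---|---|---|---|
| 50% / 50% | 0.50 | 0.500 | 0.150 | 0.150 |
| 60% / 40% | 0.60 | 0.36/0.52 = 0.692 | 0.180 | 0.208 |
| 70% / 30% | 0.70 | 0.49/0.58 = 0.845 | 0.210 | 0.253 |
| 40% / 60% | 0.40 | 0.16/0.52 = 0.308 | 0.120 | 0.092 |

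The last row reverses the assumption, and the error reverses too. In the 60%/40% row, 0.030 of the excess arises at the first survey (0.15 to 0.18) and 0.028 at the second (0.18 to 0.208). Better follow-up at 8 weeks can act only on the second part.

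**3. What an analysis could recover (60%/40% row).** Of first-survey responders, 0.6 × 0.6 + 0.4 × 0.4 = 0.52 return the second survey.
- Pairs only: 0.208.
- Two-wave mixed model with diagnosis and baseline covariates only: about 0.208 if baseline does not differ by engagement, because people with one survey then inform only the baseline mean.
- Model for change that includes usage, averaged over all first-survey responders: 0.6 × 0.30 + 0.4 × 0 = 0.18, if usage fully captures engagement.
- Change set to zero for non-returners: 0.52 × 0.208 = 0.108, which is below the true 0.18 for this group.

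None of these returns 0.15, because first-survey non-responders are absent from all of them.

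**4. Usage.** Assume 30% answer the first survey, with retention of 60% among them and 20% among the rest. All-user retention is 0.3 × 60% + 0.7 × 20% = 32%. A file of responders gives 60%. This applies only if retention is computed from CU's file after deletion.

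**5. Precision.** The 95% half-width is 1.96/√n. With 200 to 300 pairs it is 0.139 to 0.113. If 200 to 300 counted first surveys (an assumption; the documents do not say so), the results would be:
- 40% return: 80 to 120 pairs, half-width 0.219 to 0.179.
- 60% return: 120 to 180 pairs, 0.179 to 0.146.
- 80% return: 160 to 240 pairs, 0.155 to 0.127.

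**6. Timing of extra reminders.** Sign-up on the last recruitment day, 01/11/2020, plus 8 weeks is 27/12/2020. Reminders would fall on 03/01/2021 and 10/01/2021, and the project ends on 28/07/2021. Section 9.4 disposes of personal data six months from project start. If the start is taken as 12 months before the planned end (28/07/2020, an assumption), that date is 28/01/2021, or 18 days after the last reminder.

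**The case against.** Several points on the other side are good.

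- **Consent.** The participant information and consent form are embedded in the first survey, so non-responders have given only the sign-up permission. Deleting their identifiable data may be required. This stands, and the fix leaves that deletion in place.
- **Usage metrics.** A reader might infer that all usage results must describe survey responders, or that selection cannot be described once data are deleted. The documents support neither. Several section 3.2 measures are platform-level, section 8.3.2 has the developer provide usage descriptives, Diabetes UK counts traffic and referrals, and nothing says the developer's own records are erased. What remains is that the plan does not say which population each metric covers.
- **Engagement.** A reader might also infer that results will rest on the most engaged users. There are no response data to show it. Each survey carries a prize draw, the second survey accepts never having used the platform as an answer, and low users are sought for interview. Likely over-representation is as far as the text allows.
- **Sample size.** Section 8.2 says "All participants (anticipated n=200-300) will be approached to fill in a" survey before and after use, which could look like a conflict with section 8.1, where the same figure is attached to the surveys themselves. The next sentence of 8.2 expects more people to be approached, to allow for non-response. There is no contradiction.
- **Unseen material.** The second-survey invitation (Attachment 5) and the data-sharing flowchart were not available for this check. A reminder may be described there, so the point is only that sections 7, 7.1.1 and 7.2 state none.
- **Exploratory aim.** The project has no hypotheses and uses inferential statistics only where possible, so an elaborate missing-data model would be out of proportion. This stands in part: reminders and a comparison table come first, and modelling advice applies only if a model is fitted.

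**Conclusion.** The point holds in a limited form. The available text states reminders for the first survey only, and section 8.6 has no procedure for unreturned surveys. The primary change analysis followed as written is therefore an analysis of people who return both. Usage and retention computed from CU's individual-level file would exclude first-survey non-responders; whether platform-wide figures will be reported as well is left open.

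The size is unknown. Under the illustrative engagement split, a true 0.15 SD becomes 0.21 to 0.25 SD when engaged users answer more often, and 0.09 SD when they answer less often. The direction in the platform's favour is plausible but assumed. This should be corrected before recruitment because it is cheap and pairs not collected cannot be recovered. It does not invalidate an exploratory evaluation.

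**What to change.** 1. **Section 7.** Apply the same two automated Qualtrics reminders, at one and two weeks, to the second survey, and keep the unsubscribe option. Cost: one setting and up to two more emails per participant. Check that email addresses will still be held under section 9.4, particularly if recruitment is extended.

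2. **Sections 7 and 3.2.** Keep the deletion of identifiable data for first-survey non-responders. Obtain the section 3.2 usage metrics for all referred sign-ups from the developer as de-identified aggregates, where the sign-up permission allows, and report them beside the figures for survey responders. State the population for each metric. Cost: an aggregate export. The permission wording has to be checked and may need a change.

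3. **Section 8.6.** Add a procedure for surveys:
   - tabulate baseline values and Mixpanel usage for second-survey returners against non-returners;
   - in any model for change, include baseline and usage (where shared) as predictors, and average the estimate over all first-survey responders;
   - report a sensitivity analysis with change set to zero for non-returners, labelled as an assumption and not as a correction;
   - say that none of this covers people who never answered the first survey.

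   Cost: a few lines of text and one table. Participants who did not share usage need separate handling in the model. The headline change may become less favourable.
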